| Data/ Statistical Analysis For all parts of the study, the population will be people with new-onset type 2 diabetes in CPRD from 2006 (see section K, above) and the exposure will be ethnicity (either South Asian vs. European [baseline] or African Caribbean vs. European [baseline], as detailed in section L, above). Covariates in base models will include age and sex, and further covariates will be considered individually, as outlined in section vi) below. Statistical analysis is further considered by objective:   1. **Outcome**: time to initiation of first-line anti-diabetic medication, probability of receiving anti-diabetic 1 year post-diagnosis   **Entry**: date of type 2 diabetes diagnosis  **Exit**: date of first anti-diabetic prescription (defined by the absence of a prescription for the medication in the previous 6 months’ records), or end of study/ leaving CPRD practice/ death  **Analysis**: summary statistics will be compared by ethnicity using Kaplan-Meier time-to-event analysis (cumulative failure probability in a given time frame by ethnicity, comparison of medians by log-rank test), Cox proportional hazards regression models will be used to adjust for confounding/ investigate potential mediators  **Example effect measure**: hazards ratio (HR) for anti-diabetic prescription   1. **Outcome:** proportions of patients prescribed medication from each anti-diabetic (stratified by first- to third-line treatment), antihypertensive and lipid-lowering class (defined by the absence of a prescription for the medication in the previous 6 months’ records)   **Sub-population:** a) all participants starting first- to third-line anti-diabetic treatment, b) all patients on antihypertensives, or c) all patients on lipid-lowering medication  **Analysis:** proportions receiving each drug will be compared by ethnicity, then logistic regression models will be used to adjust for confounding/ investigate potential mediators  **Example effect measures**: odds ratio (OR) of being prescribed metformin (=1) vs. non-metformin medication (=0) at first stage of treatment, OR of being prescribed sulphonylurea (=1) vs. non- sulphonylurea medication (=0) at second stage of treatment, OR of calcium-channel blocking antihypertensive prescription vs. non- calcium-channel blocking antihypertensive in those on antihypertensive treatment, OR of statin prescription vs. non-statin lipid-lowering medication prescription in those with >10% 10 year cardiovascular risk   1. **Outcome:** proportions of patients prescribed each dose of each anti-diabetic, antihypertensive and lipid-lowering medication, stratified by treatment stage (defined by the absence of a prescription for the medication in the previous 6 months’ records)   **Sub-population:** a) all participants on first- to third-line anti-diabetic treatment, b) all patients on antihypertensives, or c) all patients on lipid-lowering medication  **Analysis: :** proportions receiving each dose of each drug will be compared by ethnicity, then logistic regression models will be used to adjust for confounding/ investigate potential mediators  **Example effect measures**: OR of being prescribed maximum dose (2g daily) vs. sub-maximum dose of metformin, OR of being prescribed atorvastatin 10mg per day vs. higher doses (20mg, 40mg or 80mg)   1. **Outcome:** yearly monitoring rate post commencement of medication from each anti-diabetic (first- to third-line), antihypertensive and lipid-lowering class – i.e. number of times HbA1c/ blood pressure/ blood lipids measured per person-year of follow-up, stratified by year after commencement; may be multiple entry dates per person for different medications   **Entry:** first use of any medications of interest from 2006 onwards  **Exit:** first of; end of strata (e.g. 1 year after medication commencement), end of study/ leaving CPRD practice/ death  **Analysis:** summary statistics will be compared by ethnicity, Poisson regression modelling used to adjust for confounding/ investigate potential mediators  **Example effect measures**: yearly monitoring rate ratios (RRs)   1. **Outcome:** time to medication intensification (up-titration, addition or switching) after detection of sub-optimal control of diabetes, hypertension or blood lipids, or probability of intensification 1 year post-detection of sub-optimal control; may be multiple entry dates per person for different medications   **Entry:** date when sub-optimal risk factor control detected (see section M for how this is defined for each risk factor)  **Exit:** first of; date of anti-diabetic, antihypertensive or lipid-lowering treatment intensification, end of study/ leaving CPRD practice/ death  **Analysis:** summary statistics will be compared by ethnicity using Kaplan-Meier time-to-event analysis (cumulative failure probability in a given time frame by ethnicity, comparison by log-rank test), Cox proportional hazards regression models will be used to adjust for confounding/ investigate potential mediators  **Example effect measures**: cumulative failure probability for each ethnic group 1 year post detection of sub-optimal value, comparison of median survival times using the log-rank test by ethnicity, HRs of intensification stratified by year   1. **Outcome:** influence of deprivation, polypharmacy, multi-morbidity, drug adherence (iv) and v) only), patient engagement with healthcare, diabetes duration and HbA1c on any ethnic differences found in i) to v).   **Entry:** as above for i), iv) and v)  **Exit:** as above for i), iv) and v)  **Analysis:** as above for i) to v)  **Covariates:** smoking status, BMI, deprivation, polypharmacy, multi-morbidity, drug adherence, patient engagement with healthcare, diabetes duration and HbA1c  **Effect measures:** we will observe the degree of attenuation of the ethnic difference effect measure for each outcome when each covariate is inserted in turn to models, and thus evaluate the likelihood of confounding or mediation  Sub-group/ sensitivity analyses  Analyses will be stratified by age group, and changes in guidelines and temporal trends in drug usage will be accounted for by stratifying by time.  Three sensitivity analyses will be performed – all to boost ethnicity ascertainment. Firstly, on the 58% of CPRD participants with linked secondary care data from Hospital Episode Statistics (HES) (19), using ethnicity codes from HES - present in 78% (18). Secondly, on new registrants since 2006, 78% of whom have ethnicity codes recorded (19). Thirdly, on patients from practices in the London area; where previous research indicates ethnicity recording to be approaching 60% (28).  Plans for addressing misclassification and bias  ­Plans for addressing misclassification of diabetes status and ethnicity are given above (see sections K and L respectively).  Selection bias may arise in ethnicity recording, i.e. greater recording for patients from ethnic minorities, and may also vary across time (with greater recording after the introduction of incentives in 2004) and geographically (greater in urban areas with more ethnic diversity (28) than rural ones with less). We plan to address this in three ways, as detailed above under the “sub-group/ sensitivity analyses” heading. NB/ we do acknowledge these approaches may in themselves introduce bias, and thus we will carefully compare baseline characteristics between the sensitivity and primary analysis populations.  Though primary care prescription data are almost entirely computerised, bias may be introduced into the descriptive arms of the study from unrecorded prescriptions issued in secondary care; equally medication started in secondary care and continued in primary care may falsely lengthen times to up-titration. We anticipate little bias in the monitoring outcome, where blood tests and clinical data such as blood pressure (including those recorded in secondary care) are generally automatically entered into notes via specific templates. Additionally, some bias may be present regarding the ascertainment of treatment intensification, where the intervention is non-pharmacological or constitutes referral to another service. Therefore we will also search for codes indicating lifestyle modification advice or referral which are chronologically close to the medication exposure period.  We plan to examine the influence of drug adherence in explaining any associations between ethnicity and prescribing, but this will only be measured by proxy using the proportion of days covered method; we are unable to verify whether prescriptions have been obtained from pharmacies or whether medication has been taken.  Multiple comparisons  As the study will involve multiple comparisons, findings will be interpreted with caution, and attention paid to clinically meaningful effect sizes rather than p values per se. |

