| Sample size considerations Anti-diabetic analyses  Sample sizes as per “feasibility counts” section, see table 1(below) for detectable differences in ethnic difference effect sizes. Corresponding to objective i), the proportion prescribed an anti-diabetic at 1 year post-diagnosis (42%) is taken from Sinclair et al (22) (detectable differences calculated using stpower cox command in Stata). Corresponding to objective ii), proportions prescribed metformin as first-line (73%) and a sulphonylurea as second line treatment (87%) are taken from Wilkinson et al (8) (power twoproportions command). Corresponding to objectives iv) and v), mean monitoring rate (2.45 times per year [extrapolated], assuming a SD of 2) (power twomeans command) and probability of treatment intensification at 1 year (24%) are taken from Khunti et al (23) (stpower cox command).  **Table 1. Detectable ethnic differences in outcomes.**   \| **Outcome** \| **Exposure (ethnicity): N vs. N** \| **Detectable ethnic difference effect sizes at α=0.05, β=0.90** \| \| --- \| --- \| --- \| \| Time from diagnosis to first anti-diabetic prescription \| South Asians vs. Europeans:  10.5K vs. 120.4K \| HR: 1.03 \| \| African Caribbeans vs. Europeans:  4.6K vs. 120.4K \| HR: 1.03 \| \| % prescribed metformin first-line \| South Asians vs. Europeans:  10.5K vs. 120.4K \| Difference in proportions: 1.4% \| \| African Caribbeans vs. Europeans:  4.6K vs. 120.4K \| Difference in proportions: 2.1% \| \| % prescribed sulphonylurea second-line \| South Asians vs. Europeans:  3.0K vs. 34.4K \| Difference in proportions: 2.0% \| \| African Caribbeans vs. Europeans:  1.3K vs. 34.4K \| Difference in proportions: 2.9% \| \| Mean monitoring rate, measurements per person year at risk \| South Asians vs. Europeans:  10.5K vs. 120.4K \| Rate difference: 0.07 \| \| African Caribbeans vs. Europeans:  4.6K vs. 120.4K \| Rate difference: 0.10 \| \| Time from sub-optimal diabetes control to treatment intensification \| South Asians vs. Europeans:  10.5K vs. 120.4K \| HR: 1.04 \| \| African Caribbeans vs. Europeans:  4.6K vs. 120.4K \| HR: 1.04 \| \| Time to antihypertensive initiation \| South Asians vs. Europeans:  7.6K vs. 119.4K \| HR: 1.02 \| \| African Caribbeans vs. Europeans:  3.8K vs. 119.4K \| HR: 1.02 \| \| Proportions of eligible people at high recorded CVD risk receiving statins \| South Asians vs. Europeans:  3K vs. 49K \| HR: 1.15 \| \| African Caribbeans vs. Europeans:  2K vs. 49K \| HR: 1.18 \|   Antihypertensive analyses  Sample sizes as per “feasibility counts” section. Little prior data exists in this area, but we can assume a mean time to measurement of 1 month (with an assumed SD of 1 month), as per guidelines for re-measurement after intensification (24). This would give a detectable ethnic difference in time until first monitoring as 0.04 months for South Asians vs. Europeans (using the power twomeans command in Stata), and 0.06 months for African Caribbeans vs. Europeans. Data from Petersen et al (25) suggest that 21% of those eligible for treatment for hypertension in the UK remain untreated. Adding this proportion to the expected numbers commencing antihypertensives by ethnicity (see feasibility count section), we would expect 119.4K Europeans, 7.6K South Asians and 3.8K African Caribbeans to be eligible for time to antihypertensive initiation analyses.  Lipid-lowering medication analyses  Sample sizes as per “feasibility counts” section. Assuming a mean time to monitoring of 3 months (26) and an SD of 1 month, the detectable ethnic difference in time until first monitoring would be 0.04 months for South Asians vs. Europeans, and 0.06 months for African Caribbeans vs. Europeans (using the power twomeans command in Stata). Chidwick et al reported that 24% of the high risk population received statins (21), equating to detectable ethnic differences in proportions receiving statins of HRs 1.18 and 1.15.  All detectable differences fall below what is likely to be considered clinically significant. |

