| O. Data/ Statistical Analysis For all parts of the study, the population will be people with and without new-onset type 2 diabetes active in CPRD from 2006 (see section K, above) and the exposure will be ethnicity (either South Asian vs. European [baseline] or African Caribbean vs. European [baseline], as detailed in section L, above). Covariates in base models will include age and sex, and further covariates will be considered individually, as outlined in section vi) below. Statistical analysis is further considered by objective:   1. **Outcome:** Proportion of those eligible for primary prevention who are prescribed a) antihypertensives and b) lipid-lowering medication   **Entry:** Date of incident a) hypertension Read code/ raised BP reading or b) elevated 10 year CVD risk score, at least 12 months after study start date of 1^st^ January 2005  **Exit:** First of; date of first antihypertensive/ lipid-lowering medication prescription (defined by the absence of a prescription for the medication in the previous 6 months’ records), end of study, leaving CPRD practice or death  **Analysis:** Proportions receiving antihypertensives/ statin will be compared by ethnicity, then logistic regression models will be used to adjust for confounding/ investigate potential mediators  **Example effect measure:** Odds ratio (OR) of receiving an antihypertensive/ lipid-lowering medication vs. not for each ethnic group of interest, stratified by time period since identification of hypertension/ elevated CVD risk   1. **Outcome**: time to initiation of first-line anti-diabetic/ antihypertensive/ statin, probability of receiving anti-diabetic/ antihypertensive/ statin at one year post-diagnosis/ identification of high CVD risk   **Entry**: date of type 2 diabetes diagnosis/ incident hypertension Read code or raised BP reading/ incident high 10 year CVD risk score recording  **Exit**: date of first anti-diabetic/ antihypertensive/ statin prescription (defined by the absence of a prescription for the medication in the previous 6 months’ records), or end of study/ leaving CPRD practice/ death  **Analysis**: summary statistics will be compared by ethnicity using Kaplan-Meier time-to-event analysis (cumulative failure probability in a given time frame by ethnicity, comparison of medians by log-rank test), Cox proportional hazards regression models will be used to adjust for confounding/ investigate potential mediators  **Example effect measure**: hazards ratio (HR) for anti-diabetic/ antihypertensive/ statin prescription   1. **Outcome:** proportions of patients prescribed medication from each anti-diabetic (stratified by first- to third-line treatment), antihypertensive and lipid-lowering class (defined by the absence of a prescription for the medication in the previous 6 months’ records)   **Sub-population:** a) all participants starting first- to third-line anti-diabetic treatment, b) all patients on antihypertensives, or c) all patients on lipid-lowering medication  **Analysis:** proportions receiving each drug will be compared by ethnicity, then logistic regression models will be used to adjust for confounding/ investigate potential mediators  **Example effect measures**: odds ratio (OR) of being prescribed metformin (=1) vs. non-metformin medication (=0) at first stage of treatment, OR of being prescribed sulphonylurea (=1) vs. non- sulphonylurea medication (=0) at second stage of treatment, OR of calcium-channel blocking antihypertensive prescription vs. non- calcium-channel blocking antihypertensive in those on antihypertensive treatment, OR of statin prescription vs. non-statin lipid-lowering medication prescription in those with >10% 10 year cardiovascular risk   1. **Outcome:** proportions of patients prescribed each dose of each anti-diabetic, antihypertensive and lipid-lowering medication, stratified by treatment stage (defined by the absence of a prescription for the medication in the previous 6 months’ records)   **Sub-population:** a) all participants on first- to third-line anti-diabetic treatment, b) all patients on antihypertensives, or c) all patients on lipid-lowering medication  **Analysis: :** proportions receiving each dose of each drug will be compared by ethnicity, then logistic regression models will be used to adjust for confounding/ investigate potential mediators  **Example effect measures**: OR of being prescribed maximum dose (2g daily) vs. sub-maximum dose of metformin, OR of being prescribed atorvastatin 10mg per day vs. higher doses (20mg, 40mg or 80mg)   1. **Outcome:** yearly monitoring rate post commencement of medication from each anti-diabetic (first- to third-line), antihypertensive and lipid-lowering class – i.e. number of times HbA1c/ blood pressure/ blood lipids measured per person-year of follow-up, stratified by year after commencement; may be multiple entry dates per person for different medications   **Entry:** first use of any medications of interest from 2006 onwards  **Exit:** first of; end of strata (e.g. 1 year after medication commencement), end of study/ leaving CPRD practice/ death  **Analysis:** summary statistics will be compared by ethnicity, Poisson regression modelling used to adjust for confounding/ investigate potential mediators  **Example effect measures**: yearly monitoring rate ratios (RRs)   1. **Outcome:** time to medication intensification (up-titration, addition or switching) after detection of sub-optimal control of diabetes, hypertension or blood lipids, or probability of intensification 1 year post-detection of sub-optimal control; may be multiple entry dates per person for different medications   **Entry:** date when sub-optimal risk factor control detected (see section M for how this is defined for each risk factor)  **Exit:** first of; date of anti-diabetic, antihypertensive or lipid-lowering treatment intensification, end of study/ leaving CPRD practice/ death  **Analysis:** summary statistics will be compared by ethnicity using Kaplan-Meier time-to-event analysis (cumulative failure probability in a given time frame by ethnicity, comparison by log-rank test), Cox proportional hazards regression models will be used to adjust for confounding/ investigate potential mediators  **Example effect measures**: cumulative failure probability for each ethnic group 1 year post detection of sub-optimal value, comparison of median survival times using the log-rank test by ethnicity, HRs of intensification stratified by year   1. **Outcome:** influence of deprivation, polypharmacy, multi-morbidity, drug adherence (iv) and v) only), patient engagement with healthcare, diabetes duration and HbA1c on any ethnic differences found in i) to v).   **Entry:** as above for i), iv) and v)  **Exit:** as above for i), iv) and v)  **Analysis:** as above for i) to v)  **Covariates:** smoking status, BMI, deprivation, polypharmacy, multi-morbidity, drug adherence, patient engagement with healthcare, diabetes duration and HbA1c  **Effect measures:** we will observe the degree of attenuation of the ethnic difference effect measure for each outcome when each covariate is inserted in turn to models, and thus evaluate the likelihood of confounding or mediation  Sub-group/ sensitivity analyses  See section O of original application  Plans for addressing misclassification and bias  See section O of original application  Multiple comparisons  See section O of original application |

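### Second- and third-line drug choice is compared among all starters without conditioning on the earlier drug, so a first-line ethnic difference carries into the second-line odds ratio

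*Supplement*

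**What the plan says.** The current text is the December 2019 amendment. In section O (Data/ Statistical Analysis), the choice-of-medication item sets the diabetes sub-population as "all participants starting first- to third-line anti-diabetic treatment". The result is split by line of treatment, and a class counts as newly prescribed if it is "defined by the absence of a prescription for the medication in the previous 6 months’ records". The example second-line contrast is the "OR of being prescribed sulphonylurea (=1) vs. non- sulphonylurea medication (=0) at second stage of treatment".

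On adjustment, section O states: "Covariates in base models will include age and sex, and further covariates will be considered individually". The further covariates are "smoking status, BMI, deprivation, polypharmacy, multi-morbidity, drug adherence, patient engagement with healthcare, diabetes duration and HbA1c". Section N defines polypharmacy as a count of medications, so it does not identify the earlier drug. For sub-group analyses the amendment refers back to the original application, which says "Analyses will be stratified by age group" and adds stratification by time. Nothing conditions on the preceding regimen.

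The amended null hypotheses treat first-line metformin, and the listed classes at second or third line, as proportions that might differ by ethnicity. The amended sample size section uses the "proportions prescribed metformin as first-line (73%) and a sulphonylurea as second line treatment (87"%) as baselines for Table 1.

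**The concern.** First-line choice is itself an outcome that the study expects might differ by ethnicity, and it decides who can score 1 at second line. A person taking a sulphonylurea when second-line treatment starts is a 0 in the sulphonylurea contrast because of the new-prescription rule, not because a prescriber chose something else at that point. If one ethnic group has fewer such people, its second-line sulphonylurea share is higher with no difference in how second-line treatment is chosen. A composition effect can also offset a real difference in second-line choice. The same holds at third line for any class already in use.

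The amendment's rationale is to find inequalities in prescribing and inform recommendations. A reader given a first-line OR and a second-line OR will naturally take them as two findings, when the second may be partly or wholly the first seen again.

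**Working it through.** **Inputs.** From the amended feasibility and sample size sections: metformin first-line 73%, so 27% start on something else; sulphonylurea second-line 87%; second-line numbers 34.4K European, 3.0K South Asian, 1.3K African Caribbean; two-sided α = 0.05 and power 0.90 (Table 1 labels the latter β). Not in the documents: the share of second-line starters already on a sulphonylurea.

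**The plan's own figures.** For a pooled two-proportion test with unequal groups, power = Φ((d − 1.96·SE₀)/SE₁), with SE₀ pooled and SE₁ unpooled. Solving for 90% power from 87% upward gives 2.02 and 2.95 points; Table 1 states 2.0 and 2.9. Downward it gives 2.13 and 3.20. The metformin rows also reproduce (1.45 and 2.14 against 1.4 and 2.1).

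**Mechanism.** Let s be the share of second-line starters already on a sulphonylurea and q the probability of a sulphonylurea for those not on one, equal in all groups. Then

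P(sulphonylurea at second line) = q·(1 − s).

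If s is lower by d in a minority group, the induced gap is q·d. The sign reverses if s is higher there.

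**Reading A: 87% is the share among all second-line starters.** Then q(1 − s) = 0.87. Since q cannot exceed 1, s is at most 0.13. Suppose second-line starters share the first-line mix and a fraction k of the 27% non-metformin starters began on a sulphonylurea. Then s = 0.27k, k is at most 0.13/0.27 = 0.48, and a first-line metformin gap g induces q·k·g.

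Worked case, q = 0.95 and g = 3 points: s = 1 − 0.87/0.95 = 0.084; k = 0.084/0.27 = 0.312; minority s = 0.312 × 0.24 = 0.075; minority share = 0.95 × 0.925 = 0.879. The gap is 0.9 points and OR = (0.879/0.121)/(0.87/0.13) = 1.08.

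Over q = 0.95 to 1.0 (an assumed range), with rejection rates for the unadjusted test at the planned numbers (nominal 5%):

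| First-line metformin gap | Induced second-line gap | OR | Rejection, South Asian | Rejection, African Caribbean |
|---|---|---|---|---|
| 1.4 points | 0.4-0.7 points | 1.04-1.06 | 9-18% | 6-10% |
| 2.1 points | 0.6-1.0 points | 1.06-1.10 | 16-35% | 9-18% |
| 3 points | 0.9-1.4 points | 1.08-1.14 | 28-62% | 15-32% |
| 5 points | 1.5-2.4 points | 1.15-1.26 | 65-98% | 34-74% |
| 7 points | 2.1-3.4 points | 1.22-1.40 | 92% to over 99% | about 60-97% |

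The first two rows are the plan's own first-line detectable differences. As q falls towards 0.87, s and the induced gap both go to zero, so 0.95-1.0 is the upper part of what is possible.

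**Reading B: 87% applies only to people not already on a sulphonylurea.** Then q = 0.87 and the induced gap is 0.87·d, with d the difference in prior sulphonylurea share. For d = 3 points it is 0.87 × 3 = 2.6 points. With European s varied from 5% to 27%, the OR is 1.12-1.21 and rejection is 82-96% (South Asian) and 48-70% (African Caribbean). Here d is not the metformin gap: the two are equal only if every non-metformin starter began on a sulphonylurea.

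**After conditioning.** Among people with the same earlier drug the induced gap is zero when q is equal. If 73% of second-line starters began on metformin (25.1K, 2.19K and 0.95K), detectable differences are 2.35 points upward and 2.51 downward for South Asians, and 3.42 and 3.77 for African Caribbeans. This agrees with the width factor 1/√0.73 = 1.17.

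**The case against.** The strongest reply is that the null hypothesis concerns the proportions of people prescribed each class at second or third line. That is a marginal quantity, and a gap carried over from first line is a true difference in what the groups receive. The earlier drug lies downstream of ethnicity, so conditioning on it answers a different question. This stands. A reader might infer that the plan would report a false inequality; the documents do not support that. What is missing is a statement of which quantity is meant, and an analysis that isolates the second-line choice.

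A reader might also suppose that all 27% of non-metformin starters were on a sulphonylurea. With q = 0.87, metformin shares of 73% against 76% would then give 63.5% against 66.1% at second line. But 63.5% sits badly with the plan's 87% if that describes all starters, and no document gives the split of the 27%. Those figures should not be used as the expected size.

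Three smaller points also stand. The effect measures are labelled as examples, although the sub-population is not. The outcome covers every anti-diabetic class at each line, so second-line metformin would be tabulated and the composition partly visible. A past sulphonylurea user with no prescription for six months can count as a new starter, so only current or recent users are scored 0 by rule. The original application also promises cautious interpretation by effect size. None of these separates the earlier-drug mix from the later choice.

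**Conclusion.** The gap is real and is not mended elsewhere in the plan. The all-starter second-line OR mixes the choice made at second line with the ethnic mix of earlier drugs, and cannot by itself show a separate second-line inequality. The effect arises only if that mix differs by ethnicity among people who reach second line.

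The size is uncertain because the prior sulphonylurea share is not given. If 87% describes all second-line starters, the induced gap is below Table 1's detectable differences when the first-line gap is 1.4 or 2.1 points, and becomes comparable with them at 5 to 7 points; rejection can exceed 5% well before that. If 87% describes only people not already on a sulphonylurea, the gap is 0.87 times the difference in prior share. The documents do not settle which applies. The amended reference list gives the source cited for the 87% as a study of intensification after metformin monotherapy, which would suit the second reading. That may be a renumbering slip, since the original list has a prescribing-trends study at the same number.

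Third line has the same structure, but the documents give no counts or proportions for it, so no size is claimed. This is a cheap improvement to the plan, and the marginal comparison remains valid for what it measures.

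**What to change.** - Add a second-line analysis restricted to people whose first-line drug was metformin alone, or stratified by or adjusted for first-line class, and base conclusions about second-line choice on it.
- Keep the all-starter proportions as descriptive, and say that they include differences carried over from first line.
- At third line, leave a class out of the comparison for anyone already using it, and adjust for the preceding regimen where numbers allow. Full stratification by both preceding classes is likely to be too sparse: only about 1.3K African Caribbeans are expected even at second line.
- State which population the 87% describes, and restate the second-line rows of Table 1 for the restricted population.

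The cost is wording, one extra model per contrast and some precision. If 73% of second-line starters qualify, the detectable difference rises from 2.0 to about 2.4-2.5 points for South Asians and from 2.9 to about 3.4-3.8 points for African Caribbeans, depending on direction. No new data are needed, since the prescription files already identify the earlier drug.
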